## **6.9 Concomitant treatment**

Patients will be allowed to continue to use any concomitant medications that they require except medication indexed in the exclusion criteria (as per Summary of product characteristics). If medically acceptable all concomitant medications should be kept constant during the investigation. If a change of concomitant medication is necessary, the investigator has to be informed.

Change of concomitant medication will be documented in the case report form.

## **6.10 Randomisation and unblinding procedures**

### **6.10.1 Randomisation**

At the screening visit (V0), each patient will receive the next consecutive screening number from a block of screening numbers according to their stratum (bulbar onset vs. spinal onset). Patients will be assigned to the bulbar or spinal stratum according to the location of the earliest experienced ALS symptom (defined by the first muscle weakness, or in the case of bulbar onset, by the presence of dysarthria and/or dysphagia). In the case of a patient with simultaneous onset of spinal and bulbar symptoms, onset will be defined as bulbar. Cervical and respiratory onsets are stratified to the spinal-onset stratum. This stratum assignment must be consistent with the diagnosis and clinical assessment (i.e., maximum score on bulbar scale and low score on manual muscle testing would contradict the assignment to bulbar stratum).

At the randomization visit (V1), each patient eligible for study participation will receive the next consecutive randomisation/patient number according to his stratum from a block of randomisation numbers per site. The randomisation list will be generated by Haupt Pharma Brackenheim, Germany, using a validated system, which involves a pseudo-random number generator to ensure that the resulting treatment sequence will be both reproducible and non-predictable. Study medication will be packed and blinded by Haupt Pharma Brackenheim, Germany, according to the randomisation list. Each patient medication box will be sent together with the sealed unblinding codes to the sites. The

investigator at the site takes care that each patient will be provided with the study medication box of the correct randomisation number.

### 6.10.2 Blinding

Blinding of investigator and patient is achieved by providing pioglitazone and matching placebo tablets.

The randomisation list is kept confidential by Haupt Pharma Brackenheim, Germany, and is only accessible to authorised personnel until the code is broken. At the end of the trial, any emergency opening of the envelopes will be controlled after collecting the explanations for unblinding and checking the unused treatment units. The code will be broken only at the end of the study after freezing the statistics database (by checking the data, recording any protocol violations etc.) allowing the collected data to be analysed.

### 6.10.3 Emergency procedure for unblinding

Each study site will receive sealed unblinding envelopes for emergency cases. Haupt Pharma Brackenheim will send the envelopes to the sites together with the matching medication.

In case of an emergency situation the investigator has the right to open the unblinding envelope, but every effort should be taken to avoid unblinding of patients except the information will be needed for the emergency treatment. Opened envelopes have to be signed, dated and the reason for unblinding has to be documented. The envelope has then to be filed in the patient file and the sponsor or the responsible monitor has to be informed. Unblinded patients have to be withdrawn from the study.

Additionally the sponsors' safety contact will receive a full set of sealed unblinding envelopes for emergency cases. As well every effort should be taken to avoid unblinding of patients except the information will be needed for the emergency treatment. Opened envelopes have to be signed, dated and the reason for unblinding has to be documented.

No other reason than an emergency may justify unblinding. After unblinding the investigator must note the date, time and reason on the case report form. The investigator must also immediately inform the trial monitor of the breaking of the blind.

## 6.11 Drug accountability

The investigator must keep a precise record of the dispatch and dispensing of trial medication in a drug accountability record. At all times during the study it must be possible to control that the date of dispensing and the quantity of trial medication given to each subject has been noted.

The investigator must not destroy any label or any box of medication even if only partly used. At the end of the study the investigator must group together all the boxes of used or unused treatments for recovery by the study monitor.

## 7 ADVERSE EVENTS

### 7.1 Definitions

#### 7.1.1 Adverse event (AE)

The term adverse event describes any untoward medical occurrence in a patient or a clinical investigation subject, which does not necessarily have a causal relationship with the study treatment.

This definition includes:

- Any sign or symptom occurring during the study
- Any event or disease present on the day of inclusion in the trial with symptoms that worsen during the study
- Any accident
- Any significant change in laboratory parameters
- Any reaction to drug withdrawal
- Any drug interaction
- Any effect related to overdose, abuse or dependence

This definition also applies to events occurring in any comparative group (active treatment or placebo) or during the placebo-treatment phase or during periods when the patient is not receiving any study medication.

Note: the term study treatment refers to all the drugs studied including the reference drugs and any other treatment stipulated in the protocol.

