### **Visit 1 – Baseline visit (V1)**

Patients eligible for study participation will enter the study site within 4 weeks after the screening visit and will be randomised to one of the treatment arms.

Blood samples for the determination of blood cell count, creatinine, CK, ASAT, ALAT, fasting blood glucose, and pioglitazone baseline level will be obtained. A physical examination, ALS FRS-R, and EuroQol EQ-5D will be performed. The patient will receive study medication according to the randomization list and a study participant card (see appendix IX).

Any changes in the concomitant medication and adverse events before and during visit 1 will be documented.

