## **7.2 Monitoring and recording of adverse events**

At each visit after V0 the investigator must question the patient about the occurrence of any adverse event and note any abnormal laboratory findings. A neutral question such as "since the last visit have you felt any untoward or unusual symptoms other than those related to your illness?" elicits any adverse events experienced by the patient.

Whatever the relation to the study treatment is, any adverse event such as those described in section 7.1 spontaneously reported by the patient or observed by the investigator must be reported on the appropriate page of the case report form. For each adverse event, the following information should be documented:

- Description of the event (diagnosis and symptoms in verbatim terms)
- Outcome
- Seriousness
- Duration (start date and stop date)
- Severity (mild, moderate or severe); see section 7.1.4
- Frequency (permanent, intermittent)
- Causal relationship with the study treatment according to the scale shown in section 7.3
- Corrective actions including measures taken for the study treatment

The study number, patient number and investigator's signature must also be noted.

Any clinically significant event including any abnormal laboratory result or vital sign must be followed-up until it has completely disappeared or the investigator has assessed its sequelae, even after the end of the study.

The results of any complementary tests performed (laboratory tests, ECG, X-rays etc.) must be dated and appended to the CRF. The investigator must evaluate each adverse event and give his/her opinion about the causal relationship with the drug(s) used.

A period of 14 days for follow up of AEs after the patient has routinely or prematurely terminated the study seems sufficient.

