### 8.2.6 Safety evaluation

The full-analysis set will be used to address issues of safety. Adverse events data will be processed in the statistical analysis after coding according to the MedDRA dictionary.

Adverse events (AEs) will be classified as pre-treatment AEs or treatment-emergent AEs. Analyses will be performed for these classes. Pre-treatment AEs are defined to be AEs, which obviously occurred prior to the first administration of study medication. Treatment-emergent AEs are defined to be AEs, which occurred at or after the first administration of study medication. In case of doubt regarding the timing of AE onset the worst-case scenario will be applied, i.e. the AE will be considered as treatment-emergent.

AEs will be analysed regarding their seriousness, severity, outcome and causality assessment. SAEs will be analysed regarding their severity, outcome and causality assessment. Furthermore, all AEs with possible, probable or definite causal relationship to study medication (causality assessment) will be summarised as 'drug-related' AEs. They will be analysed regarding severity and outcome. All analyses will report frequency counts of subjects by MedDRA SOC and preferred term. Furthermore, treatment-emergent AEs will be presented by preferred term and sorted by frequency.

Listings by subject will be provided for SAEs and for AEs.

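### Section 8.2.6 classes adverse events by time of occurrence only, with no rule for worsening after the first dose, so some aggravated events can be missing from the treatment-emergent tables

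*Protocol*

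**What the plan says.** Section 7.1.1 lists what counts as an AE. One item is "Any event or disease present on the day of inclusion in the trial with symptoms that worsen during the study", so worsening is enough to make a pre-existing condition an AE.

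Section 8.2.6 fixes two analysis classes. The earlier class is set out in these words: "Pre-treatment AEs are defined to be AEs, which obviously occurred prior to the first administration of study medication". The later class, on which the main safety tables rest, has its own sentence: "Treatment-emergent AEs are defined to be AEs, which occurred at or after the first administration of study medication". The section adds a rule for unclear cases, "In case of doubt regarding the timing of AE onset the worst-case scenario will be applied", which sends them to the treatment-emergent class. Of the two classes it says "Analyses will be performed for these classes", and it plans a further table of treatment-emergent AEs by preferred term in order of frequency.

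On recording, section 7.2 asks for "Duration (start date and stop date") and for a severity for each AE. Events before dosing are collected: under the baseline visit in section 5.3, "Any changes in the concomitant medication and adverse events before and during visit 1 will be documented". The serious adverse event form in Appendix V asks for the date on which symptoms began. No section asks for a date of worsening, or for a new entry when an existing event worsens.

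**The concern.** The AE definition recognises aggravation, but the rule that sorts AEs for analysis does not. A treatment-emergent table is meant to show what appeared or got worse on treatment. If a known pre-dose start decides the class, an event that study drug makes worse is grouped with events that had nothing to do with the drug.

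Tolerability and safety are secondary objectives. The expected events in section 2.3 include oedema, fatigue, leg cramps and myalgia. Where a patient already has such a symptom before the first dose, a drug effect would show as aggravation rather than as a new event. The treatment-emergent tables could then under-count it. The class boundaries are written into the protocol itself, so this is not simply a detail left to the statistical analysis plan.

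**Working it through.** No arithmetic applies, because the point concerns a definition. The check is to run the possible clinical courses through sections 7.1.1, 7.2 and 8.2.6 together.

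Timing first. The schedule in the trial summary labels V1 as inclusion. Section 5.3 puts V1 within 4 weeks of screening and has study medication handed out there. AE questioning applies at each visit after V0 (section 7.2). So there is a window of up to about 4 weeks between consent and first dose in which an AE can start, and worsening after inclusion is in practice mostly worsening on treatment.

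- **Course (a): an AE starts between consent and first dose, is recorded with that start date, and worsens on study drug.** The start is known, so the rule for doubtful timing does not apply. The event occurred before the first dose and nothing in section 8.2.6 moves it. As written it is pre-treatment.
- **Course (b): a condition present at inclusion worsens on study drug, and the investigator dates the AE at the worsening.** It occurred after the first dose and is treatment-emergent. There is no problem.
- **Course (c): the same condition worsens, but the investigator enters the original onset as the start date.** It is pre-treatment.

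Courses (b) and (c) are clinically the same. The protocol does not choose between them, so two sites can file the same course in different classes.

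Where the affected events still appear:

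| Output in section 8.2.6 | Event in course (a) or (c) |
|---|---|
| Treatment-emergent analyses, including the table ordered by frequency | Absent |
| Analyses of the pre-treatment class | Present, mixed with events that did not change on drug |
| Drug-related summary, worded for "all AEs with possible, probable or definite causal relationship to study medication" | Present if judged related |
| Subject listings of AEs and serious AEs | Present |

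Size. If a share f of the new-or-worsened cases of an event is filed as pre-treatment, a true incidence p appears in the treatment-emergent table as p × (1 − f). With the same f in both arms, a true difference d appears as d × (1 − f). If all worsenings are dated as in (b) and no event follows course (a), f is zero. The protocol gives neither the prevalence of these symptoms before dosing nor the share that would worsen, so f cannot be filled in.

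**The case against.** The strongest reply is that the two sections fit together when read in sequence. Under section 7.1.1 a condition present at inclusion becomes an AE only through its worsening; until then it is medical history or a concomitant disease. The worsening is then the AE, it normally happens after the first dose, and section 8.2.6 makes it treatment-emergent. This is a natural reading, and it means that misfiling of baseline conditions is possible but not automatic.

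The same argument can be tried on course (a), since the item in section 7.1.1 covers events as well as diseases: the later worsening would be an AE of its own. But here an AE record with a known pre-dose start already exists. Section 7.2 does not forbid a second entry, but does not ask for one either, and without it section 8.2.6 leaves the event in the pre-treatment class. The window is also short, which limits how many events are affected.

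A reader might infer that aggravated events drop out of the drug comparison altogether. The protocol does not support that: both classes are analysed, the drug-related summary is worded for all AEs, and AEs and serious AEs are listed by subject. The pre-treatment table is still a weak substitute, because it does not separate aggravated from unchanged events.

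A reader might also cite raised liver enzymes, creatine kinase or anaemia as signals that would be lost. That does not follow either. Section 7.1.1 makes a significant laboratory change an AE trigger of its own, Table 5.1 schedules ASAT, ALAT and CK at every visit from V0 to V6 and blood counts at all of these except V2, and section 3 has laboratory values compared across treatment groups.

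Finally, handling of grade changes is often settled in form instructions or the statistical analysis plan, to which section 8.2 defers further detail. That may happen here, but it would have to alter a definition that the protocol has already fixed. If a site has not recorded when an event worsened, the date may not be recoverable later.

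**Conclusion.** The point holds in a limited form. Section 8.2.6 defines the classes by time of occurrence alone, although section 7.1.1 treats worsening as an AE. As written, an AE with a known start between consent and first dose that worsens on drug is pre-treatment, and a worsened baseline condition can be classed either way. The consequence is possible under-counting of aggravated symptoms in the treatment-emergent tables.

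The documents do not support calling the two sections irreconcilable, or claiming a bias of a stated size in the safety comparison. The conclusion rests on two things: that some symptoms are present before dosing and worsen afterwards, and that at least some sites keep the earlier start date. The protocol permits both and quantifies neither. This is an inexpensive improvement that should be made before data are collected.

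**What to change.** In section 8.2.6, define treatment-emergent AEs as those that start at or after the first dose, or that were present before it and worsen in severity or seriousness at or after it. Keep the pre-treatment class for events that start before the first dose and do not worsen afterwards. Leave the existing rule for doubtful timing in place.

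In section 7.2, require a worsening to be entered as a new AE line with its own start date and severity, so that the definition can be applied from the data and in the same way at all sites.

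The cost is two sentences, a completion note for the case report form, and slightly more treatment-emergent AEs in both arms. Neither the AE definition in section 7.1.1 nor any clinical procedure changes.

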#### 7.1.2 Serious adverse event (SAE)

A serious adverse event is any untoward medical occurrence that at any dose:

- Results in death,
- is life-threatening,
- requires in-patient hospitalisation or prolongation of existing hospitalisation,
- results in persistent or significant disability/incapacity,
- is a congenital anomaly, birth defect, or
- may require intervention, as a medically important event, to prevent one of the above criteria or may expose the patient to danger, even though the event is not immediately life threatening or fatal or does not result in hospitalisation (examples: allergic bronchospasm treated on an outpatient basis, convulsions not requiring hospitalisation or abnormal laboratory parameters compromising patient safety).

The following points should be taken into account when evaluating the seriousness of an adverse event:

- The life-threatening criterion indicates that there was an immediate risk of death at the time of its occurrence. This does not mean that if the adverse event had occurred in a more severe form it would have lead to death.

The following are not considered to be serious adverse events:

- An event causing a brief visit to a hospital consultation, an open-door or day hospital,
- outpatient treatment in the emergency department although the reason for which this treatment was instituted may be serious, or
- admission to hospital (more than one night in a hospital bed) including surgical operations planned before or during the study if the condition was present before the study and provided that it does not worsen during the study.

The following are considered to be serious adverse events even if they do not comply with the definition:

- Adverse events caused by misuse or overdose,
- Any pregnancy discovered during the study.

Note: a state of pregnancy is an exclusion criterion. Hence contraceptive measures are necessary in women with childbearing potential throughout the study. However if pregnancy is discovered during the study the trial treatment must immediately be discontinued and the pregnancy followed to term.

N.B. a non-serious adverse event designates any other event not corresponding to the above-defined criteria.

### 7.1.3 Non Serious Adverse Events

Non serious adverse events mean adverse event, which are not categorised as serious adverse event.

### 7.1.4 Severity (Intensity) and outcome

The severity of an adverse event represents the intensity of the event as reported by the patient or assessed by the investigator. It does not reflect the clinical seriousness of the event (for example severe nausea, minor stroke). The intensity is evaluated independently from the relation to the study treatment.

- Mild: the adverse event is transient and easily tolerated by the patient.
- Moderate: the adverse event causes the patient discomfort and interference with the patient's usual activities.
- Severe: the adverse event causes considerable interference with the patient's usual activities

The outcome of each AE must be assessed according to the following classification:

|                                  |                                                                                                         |
|----------------------------------|---------------------------------------------------------------------------------------------------------|
| - completely recovered :         | The patient has fully recovered with no observable residual effects                                     |
| - not yet completely recovered : | Improvement in the patient's condition has occurred, but the patient still has some residual effects    |
| - deterioration :                | The patient's overall condition has worsened                                                            |
| - permanent damage :             | The AE has resulted in a permanent impairment                                                           |
| - death :                        | The patient died due to the AE                                                                          |
| - ongoing :                      | The AE has not resolved                                                                                 |
| - unknown :                      | The outcome of the AE is not known because the patient did not return for follow-up (lost to follow-up) |

## **7.2 Monitoring and recording of adverse events**

At each visit after V0 the investigator must question the patient about the occurrence of any adverse event and note any abnormal laboratory findings. A neutral question such as "since the last visit have you felt any untoward or unusual symptoms other than those related to your illness?" elicits any adverse events experienced by the patient.

Whatever the relation to the study treatment is, any adverse event such as those described in section 7.1 spontaneously reported by the patient or observed by the investigator must be reported on the appropriate page of the case report form. For each adverse event, the following information should be documented:

- Description of the event (diagnosis and symptoms in verbatim terms)
- Outcome
- Seriousness
- Duration (start date and stop date)
- Severity (mild, moderate or severe); see section 7.1.4
- Frequency (permanent, intermittent)
- Causal relationship with the study treatment according to the scale shown in section 7.3
- Corrective actions including measures taken for the study treatment

The study number, patient number and investigator's signature must also be noted.

Any clinically significant event including any abnormal laboratory result or vital sign must be followed-up until it has completely disappeared or the investigator has assessed its sequelae, even after the end of the study.

The results of any complementary tests performed (laboratory tests, ECG, X-rays etc.) must be dated and appended to the CRF. The investigator must evaluate each adverse event and give his/her opinion about the causal relationship with the drug(s) used.

A period of 14 days for follow up of AEs after the patient has routinely or prematurely terminated the study seems sufficient.

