Expected Adverse Events: Anaemia, back pain, cardiac failure, CPK increased, fatigue, headache, haematocrit decreased, haemoglobin decreased, hepatic congestion, hepatocellular dysfunction, LDH increased, leg cramps, liver enzymes increased, myalgia, pharyngitis, oedema (generalised and peripheral), RBC decreased, sinusitis, tooth disorder, upper respiratory tract infection, urinary tract infection, weight increased, resumption of ovulation, vision abnormal, flatulence

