### **3 STUDY PURPOSE, TRIAL OBJECTIVES AND ENDPOINTS**

As the efficacy of riluzole to prolong survival in ALS is limited, there is an urgent need to identify other compounds and to evaluate their potential in clinical studies. The pharmacological profile of pioglitazone suggests that this compound may be effective in slowing down the neurodegenerative process observed in ALS and it is therefore important to study this drug in ALS patients. As a significant percentage of patients with ALS will receive riluzole, the study population will consist of patients stabilised on standard riluzole therapy at time of inclusion. After completing this study, patients may have the option to participate in another planned, longer, safety study with pioglitazone.

This study will evaluate the efficacy, safety and tolerability of pioglitazone (45 mg/day) versus placebo in patients with ALS receiving standard, approved therapy (riluzole, 50 mg bid). Mortality defined exclusively as death represents the primary endpoint. Secondary efficacy endpoints will include incidence of tracheotomy or non-invasive ventilation (NIV), ALS Functional Rating Scale (ALSFRS-R; the revised version including the respiratory parameters) and measurement of quality of life using the Euroqol EQ-5D. Assessment of clinical tolerability and safety will be performed by comparison of findings on physical examination, adverse events incidence, and clinical laboratory values across treatment groups.

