#### **4.3.1 Inclusion criteria**

To be considered eligible to participate in this trial a patient must meet the inclusion criteria listed below.

- Possible, probable (clinically or laboratory) or definite ALS according to the revised version of the El Escorial World Federation of Neurology criteria
- Disease duration more than 6 months and less than 3 years (inclusive). Disease onset defined as date of first muscle weakness, excluding fasciculation and cramps
- Best-sitting SVC between 50 % and 95 % of predicted normal
- Continuously treated with 100 mg riluzole daily, for at least 3 months
- Capable of thoroughly understanding all information given and giving full informed consent according to GCP
- Women of childbearing age must be non-lactating and surgically sterile or using a highly effective method of birth control and have a negative pregnancy test. Acceptable methods of birth control with a low failure rate i.e. less than 1% per year) when used consistently and correct are such as implants, injectables, combined oral contraceptives, hormonal intrauterine devices (IUDs), or double-barrier methods (condom or diaphragm with spermicidal agent or IUD), sexual abstinence or vasectomised partner.
- Onset of progressive weakness within 36 months prior to study

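### The model adverse-event question in section 7.2 leaves out symptoms the patient puts down to ALS, which contradicts the AE definition in 7.1.1 and may cause partial under-recording of expected drug effects

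*Protocol*

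**What the plan says.** Section 7.2 first states a general duty: "At each visit after V0 the investigator must question the patient about the occurrence of any adverse event and note any abnormal laboratory findings". It then introduces a model wording with "A neutral question such as", and the wording that follows is "since the last visit have you felt any untoward or unusual symptoms other than those related to your illness". The section says that such a question brings out any adverse events the patient has had. It is the only wording the protocol supplies. The next paragraph of 7.2 requires recording, whatever the relation to study treatment, of any adverse event described in 7.1 that is "spontaneously reported by the patient or observed by the investigator must be reported on the appropriate page of the case report form".

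The definition in 7.1.1 includes "Any sign or symptom occurring during the study" and, separately, a disease already present at inclusion whose symptoms worsen. It contains no exception for ALS.

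Under 7.3.1 the investigator assesses causality for serious and non-serious events. The lowest of the four categories covers events reasonably explained by underlying disease. The category above it, possible, covers events for which drug and disease may both be responsible.

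Section 3 makes tolerability an objective, to be judged by comparing examination findings, "adverse events incidence, and clinical laboratory values across treatment groups". Section 8.2 says that safety parameters are reported descriptively.

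**The concern.** The example asks the patient to decide first what is due to ALS and to report only the rest. That is a causality judgement made by the person least able to make it, before anything is written down. It removes part of what 7.1.1 defines as an adverse event, so the label neutral does not fit.

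This matters because the protocol's own list of expected drug effects in section 2.3 contains subjective muscle and general symptoms. It lists "hepatic congestion, hepatocellular dysfunction, LDH increased, leg cramps, liver enzymes increased, myalgia", and also fatigue and back pain. A patient with a progressive motor disease has an obvious alternative explanation for new or worse cramps, tiredness or muscle pain. If these go unmentioned, they never reach the investigator's assessment in 7.3 or the drug-related AE tables in 8.2.6, where events rated possible are counted. At stake is the tolerability comparison named as an objective in section 3.

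**Working it through.** **Text comparison**

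| Step | What the protocol provides | What the example question does |
|---|---|---|
| Scope of an AE (7.1.1) | Any sign or symptom; worsening of existing disease counts | Leaves out what the patient relates to the illness |
| Who judges underlying disease (7.3.1) | The investigator, after recording | The patient, before recording |
| Ambiguous cause (7.3.1, 8.2.6) | May be rated possible, then counted as drug-related | May never be recorded |

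The overlap between drug effects and disease is visible in the protocol, though only in part. Cramps appear among the expected effects in 2.3. Section 4.3.1 names them when it defines onset: "Disease onset defined as date of first muscle weakness, excluding fasciculation and cramps". That clause keeps cramps out of the onset date, but there would be no need to mention them unless they could accompany early ALS. For fatigue, myalgia and back pain the protocol gives no such link. That patients may ascribe them to ALS is an assumption, though a reasonable one.

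**Illustration of size**

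The protocol states no AE rate, capture rate or safety power, so there is no figure to reproduce. The only input from the document is 110 patients per arm (section 1). All rates below are assumed.

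Let p0 be the background incidence of a symptom, d the excess caused by the drug, s0 the share of background cases recorded and s1 the share of excess cases recorded. Because patient and investigator are blinded, take the same shares in both arms. Then:

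- recorded placebo incidence = p0·s0
- recorded pioglitazone incidence = p0·s0 + d·s1
- recorded difference = d·s1
- recorded ratio = 1 + (d·s1)/(p0·s0)

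The difference shrinks whenever s1 is below 1. The ratio is unchanged if s1 = s0, rises if s1 > s0 and falls if s1 < s0.

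To show the chance of noticing a signal, the last column uses the two-proportion normal approximation at a nominal two-sided 5%: z = [difference − 1.96·√(2p̄(1−p̄)/n)] / √{[pA(1−pA) + pB(1−pB)]/n}. Here n = 110, pA and pB are the recorded incidences and p̄ is their mean. For 10% versus 17.5%: z = (0.075 − 1.96 × 0.0464)/0.0462 = −0.35, which gives 0.36.

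| Assumed true 20% vs 35% | Recorded | Difference (points) | Ratio | Chance of p < 0.05 |
|---|---|---|---|---|
| s0 = s1 = 1 | 20% vs 35% | 15.0 | 1.75 | 0.71 |
| s0 = s1 = 0.8 | 16% vs 28% | 12.0 | 1.75 | 0.58 |
| s0 = s1 = 0.5 | 10% vs 17.5% | 7.5 | 1.75 | 0.36 |
| s0 = s1 = 0.3 | 6% vs 10.5% | 4.5 | 1.75 | 0.23 |
| s0 = 0.3, s1 = 0.8 | 6% vs 18% | 12.0 | 3.0 | 0.79 |
| s0 = 0.8, s1 = 0.3 | 16% vs 20.5% | 4.5 | 1.28 | 0.14 |

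Other assumed rates show the same pattern when equal capture falls from 1 to 0.3. For 10% versus 20% the difference goes from 10 to 3 points and the chance from 0.55 to 0.19. For 40% versus 55% the difference goes from 15 to 4.5 points and the chance from 0.61 to 0.16.

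**The case against.** Several points on the other side are sound.

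- **It is an example.** The words that introduce it make it illustrative, and the binding sentence before it covers any adverse event. A reader might infer that the wording is a mandatory script used at every visit and telephone contact. The protocol does not say so, and no CRF script is shown. What remains is that a model question which contradicts the definition is an error in the document, and that the approximately 16 sites are offered no other.
- **Other recording routes remain.** Spontaneous reports and investigator observation must be recorded. CK, liver enzymes, blood count, weight and physical examination do not depend on the question. The schedule collects AEs at the four telephone contacts without examination or laboratory tests, but a site visit with examination follows each one. A reader might infer that ALS-like drug effects are lost altogether; the text does not support that. These routes are weaker, however, for fatigue, cramps and muscle pain, which a laboratory test or examination will not reliably show.
- **The direction is not fixed.** A reader might infer that the comparison is biased towards no difference. Under equal capture the ratio does not move. If background ALS symptoms are left out more often than drug-caused ones, the ratio rises and the chance of seeing a signal can rise too (0.79 against 0.71 above). Only the shrinkage of the absolute difference holds generally, and only where some drug-caused cases go unrecorded.
- **No safety test is planned.** Safety is descriptive, so the power column is only a gauge of visibility.
- **Committee oversight.** The monitoring committee is informed of SAEs and has unblinded data. Deaths and hospital admissions do not depend on this question.

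**Conclusion.** The point holds as an inconsistency with a limited consequence. The only model question in 7.2 excludes events that 7.1.1 includes, and it moves the judgement on underlying disease from the blinded investigator to the patient. Sites that adopt it may under-record subjective expected effects such as leg cramps, fatigue and myalgia.

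The loss is partial. It can reduce the absolute between-arm difference in recorded incidence; the effect on the ratio is nil under equal capture and of either sign otherwise. The size cannot be derived from the protocol. The illustration rests on assumed incidences, assumed capture shares and the same shares in both blinded arms. The primary endpoint, death, is not affected. The change is worth making because it is cheap and serves a stated objective, but the trial's main conclusion does not depend on it.

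**What to change.** In section 7.2, replace the example with an open question that drops the exclusion and asks about worsening, for instance: *Since your last visit, have you noticed anything untoward or unusual, or has any symptom become worse?* Record the answers as 7.1.1 already requires, and let the blinded investigator assign the relation to ALS or to the drug under 7.3.

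The change is one sentence, with no extra visits, tests or staff. The cost is more AE entries and coding, many of them ALS progression. Those entries add background events in both arms, which can make a drug effect harder to see in the overall AE counts. That burden already follows from the definition in 7.1.1, and the causality categories in 7.3.1 allow such events to be separated in the tables.
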